**Activity**						
MPHTJP test^a^		**×**				
conventional treatment			**×**	**×**	**×**	**×**
Acupuncture(LA/HA group^b^)			**×**	**×**	**×**	
Compensatory acupuncture (Control group)						**×**
**Assessment**						
HRQOL^c^	FACT-Ga^d^		**×**	**×**	**×**	
Symptoms	mESAS^e^		**×**	**×**	**×**	
AEs/SAEs^f^	NCI-CTCAE^g^ V4.0		**×**	**×**	**×**	
Blood test indexes	MDSCs^h^	**×**			**×**	
	Tregs^i^					
	CTC^j^					

^a^MPHTJP test: Measuring pain heat threshold of Jing point and presented in the online supplementary appendix

^b^LA/HA group: Low dose acupuncture/High dose acupuncture group

^c^HRQOL: Health-related quality of life

^d^FACT-Ga: Functional Assessment of Cancer Therapy – Gastric scale

^e^mESAS: Modified Edmonton Symptom Assessment Scale

^f^AEs/SAEs: Adverse events/Severe adverse events

^g^NCI-CTCAE: National cancer institute common terminology criteria for adverse events

^h^MDSCs: Myeloid-derived suppressor cells

^i^Tregs: Treg cells

^j^CTC: Circulating tumor cells

### Safety assessment

Although acupuncture is a relatively safe treatment with a low risk of adverse events [43], any adverse events (AEs) during the study period will be assessed, treated, and documented in the case report form (CRF). AEs, such as broken needle, localized hematoma, bleeding, or localized severe sharp pain will be categorized as acupuncture treatment-related; AEs such as chemotherapy-related or surgical treatment-related will be categorized as non-acupuncture treatment-related. Severe adverse events (SAEs) occurred in any of the three groups would be reported to the independent ethics committee. The ethics committee will conduct an annual follow-up review of this study.

### Quality control

To ensure consistency of the study, research staff in recruitment sites will receive extensive training from the principal investigator ([name]) concerning the protocol, manipulating methods of acupuncture and follow-up of participants. Additionally, the same participants should be taken charge of by the same research assistant/outcome assessor throughout the trial. They will instruct participants to complete HRQOL and symptoms questionnaires, explain the contents of questionnaires if necessary and remind the participants of their schedule by phone or WeChat. On each outcome assessment visit, the forms will be collected and examined by outcome assessors and recorded in CRF in time.

### Data management

All the data collected will be documented in CRF first by clinical research coordinators and checked by 2 trained clinical research associates before double data entry into EDC system by trained research assistant. This rule is set to ensure the data is accurate, authentic, and traceable. The database will be protected by a password, and only the principal investigator will have access to the final dataset. A data monitoring committee that is independent of researcher and sponsor and has no conflict of interest with this study will be estimated. It will be responsible for the management of data quality.

### Sample size

In our pilot trial, the total AUCs of FACT-Ga TOI during the 3 cycles of chemotherapy were 5402 and 4780 in the acupuncture and control groups, respectively, with a standardized derivation of 1109 [27]. Thus, a total of 62 participants will be needed in each arm to detect a significant difference between the control group and either LA or HA group, with an α of 0.025 and a power of 80%. Considering the total dropout rate of 22.41% in our pilot study and eliminating the impact of COVID-19 epidemics, we plan to enroll a total of 249 patients to allow a dropout rate of 25%.

### Statistical analysis

Full Analysis Set (FAS): FAS will be composed of all randomized subjects according to the intention-to-treat analysis (ITT) principle, excluding those with the following criteria: (1) patients who request to withdraw from the study and provide an informed statement that he/she does not want to be analyzed, (2) patients who do not meet the inclusion/exclusion criteria incorrectly included when random, and (3) patients who are only with baseline data, without any data after chemotherapy in this trial.

Per-protocol Set (PPS): PPS will be composed of patients who complete at least 50% treatment according to the protocol which is defined as: (1) no less than 3 cycles of chemotherapy; (2) no less than 2 cycles of acupuncture treatment with no less than 50% acupuncture treatment for per cycle (i.e., no less than 4 times acupuncture in HA group and 2 times acupuncture in LA group);

FACT-Ga and mESAS scales score, demographics data, baseline clinical characteristics, the other efficacy indicators and safety indicators will be analyzed and compared in FAS. Sensitivity analysis of FACT-Ga and mESAS scales score will be used in PPS.

Numerical data are expressed as proportions, rates and frequencies. Continuous data are presented as the mean standard deviation for normal distribution, or the median and 25 ~ 75% percentile for other distributions.

We will modify our analyses to compare the outcomes in the FAS population; we will also compare the differences in the PPS population as sensitivity analysis. Missing data will be imputed using the worst observation carried forward (WOCF) method to calculate the AUC. We will use student’s t-test, analysis of variance (ANOVA) with least significant difference (LSD) for post hoc test and baseline score as covariate, χ2 test, or Fisher’s exact test to test the differences among groups. In addition, the average and the worst score of the FACT-Ga and mESAS scale during the chemotherapy will use the same statistical method. Demographics data, baseline clinical characteristics, and the other outcomes will be reported and compared using χ2 test or Fisher’s exact test. All hypothesis tests in this study are 2-sided tests, with an alpha < 0.05. Data will be analyzed using SPSS 17.0 and Stata 11.0 software.

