According to our pilot trial, the effect of EA should persist throughout the whole phase of the intervention, rather than at any specific time point [27]. Therefore, the standardized area under curve (AUC, 21days/cycle×3 cycles), calculated by linear interpolation, will be used to reflect the repeated measures of HRQOL (FACT-Ga) and symptom burden (mESAS) during the intervention period [41, 42]. Furthermore, we hypothesized that the effect of EA will be mainly reflected on the TOI scores, which regards more with gastric cancer.

The other pre-specified outcomes include blood test indexes (concentration of circulating myeloid-derived suppressor cells, concentration of circulating Treg cells, and the number of circulating tumor cells), the incidence of treatment-emergent adverse events defined as any adverse events happened after randomization. The severity is validated using national cancer institute common terminology criteria for adverse events (NCI-CTCAE) V4.

The outcome assessments will be performed by outcome assessors at the inpatient department of each participating site. All the outcome assessors will be trained in conducting interviews and performing measurements before the study begins and will follow a standard protocol. The schedule of measurements is presented in Table 1.

**Table 1 Tab1:** Measurements to be taken at each point in the trial

Period		Screening	1st cycle	2nd cycle	3rd cycle	4-6th cycle
Timeline		D-21-0	D1-21	D1-21	D1-21	
**Enrolment**		**×**				

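### Safety and efficacy are both analysed in a set described as intention-to-treat that removes ineligible and baseline-only patients after allocation

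*Protocol article*

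**What the plan says.** All analysis-set rules are in the Statistical analysis section of the protocol article.

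- **Definition of the FAS:** "FAS will be composed of all randomized subjects according to the intention-to-treat analysis (ITT) principle, excluding those with the following criteria". Three groups are then removed:
  1. Exclusion 1, refusal of data use: "patients who request to withdraw from the study and provide an informed statement that he/she does not want to be analyzed"
  2. Exclusion 2, ineligibility found later: "patients who do not meet the inclusion/exclusion criteria incorrectly included when random"
  3. Exclusion 3, nothing beyond baseline: "patients who are only with baseline data, without any data after chemotherapy in this trial"
- **Use of the FAS:** questionnaire scores, baseline data and the remaining outcomes all go to this set: "the other efficacy indicators and safety indicators will be analyzed and compared in FAS".
- **The only other set:** the per-protocol set (PPS), which requires a minimum of chemotherapy and acupuncture. Its role is limited to the scores: "Sensitivity analysis of FACT-Ga and mESAS scales score will be used in PPS".

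The article names no separate safety population. Under Secondary outcomes, the safety measure is "the incidence of treatment-emergent adverse events defined as any adverse events happened after randomization". The Safety assessment section has every adverse event in the study period recorded in the case report form, and severe events in any arm reported to the ethics committee.

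**The concern.** Exclusions 2 and 3 act after allocation, and the resulting set carries both the harms and the benefit comparison.

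**Safety.** An ineligible patient may receive the full course (21 sessions in the high-dose arm, 9 in the low-dose arm) and still have every adverse event left out of the comparison. A patient with an event between randomisation and the start of chemotherapy, and no data afterwards, is also left out. The population for the safety table is therefore narrower than the adverse-event definition implies.

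**Efficacy.** The trial is open-label and its primary endpoint is patient-reported. Leaving before any post-baseline score can depend on which arm the patient was given. So can a later finding of ineligibility: the exclusion rule does not say when or by whom it is decided, or whether the decision is made without knowledge of the arm. Two criteria in the Participants section are easy to reassess in hindsight, namely the ability to complete the questionnaires and the plan for at least three chemotherapy cycles.

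**Working it through.** **1. The planned denominator (Sample size section).** Inputs: AUC means 5402 and 4780, SD 1109, α 0.025, power 80%, dropout 25%.

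- Difference: 5402 − 4780 = 622.
- Per arm, normal approximation, two-sided: 2 × (2.241 + 0.842)² × (1109/622)² ≈ 60.4, so 61. The t-based calculation gives 61.7, so 62, as stated.
- With dropout: 62/0.75 = 82.7, so 83 per arm and 3 × 83 = 249, as stated.

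The sample size is not at issue. It fixes the all-randomised denominator at 83 per arm.

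**2. Who leaves the safety comparison.** I read exclusion 3 as meaning no data once chemotherapy has begun.

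| Patient | In FAS? | Events in the comparison? |
|---|---|---|
| Ineligible, treated, followed | No (exclusion 2) | Lost |
| Event between randomisation and chemotherapy, no later data | No (exclusion 3) | Lost |
| Event in first days of chemotherapy, no questionnaire afterwards | Depends on whether an adverse-event record counts as data | Kept if it does, lost if not |
| Leaves early with at least one later score | Yes; gaps filled by worst observation carried forward | Kept |
| Refuses use of data | No (exclusion 1) | Lost, legitimately |

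The first two rows follow from the text. The third depends on the reading. The PPS restores nobody.

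**3. How many.** The documents give no count. The pilot dropout of 22.41% would be 0.2241 × 249 ≈ 56 patients. That is a ceiling for early leavers, because dropouts with some later data stay in the FAS. It says nothing about how many will be found ineligible.

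**4. Effect on an event rate (all risks assumed).** With k of 83 removed, risk p among the removed and r among those kept, the all-randomised rate is [k·p + (83 − k)·r]/83, while the FAS shows r.

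| k | r | p | All randomised | FAS | Expected events lost |
|---|---|---|---|---|---|
| 4 | 20% | 50% | (2.0 + 15.8)/83 = 21.4% | 20.0% | 2.0 |
| 8 | 20% | 50% | (4.0 + 15.0)/83 = 22.9% | 20.0% | 4.0 |
| 4 | 20% | 20% | (0.8 + 15.8)/83 = 20.0% | 20.0% | 0.8 |
| 8 | 20% | 20% | (1.6 + 15.0)/83 = 20.0% | 20.0% | 1.6 |
| 4 | 10% | 50% | (2.0 + 7.9)/83 = 11.9% | 10.0% | 2.0 |
| 8 | 10% | 50% | (4.0 + 7.5)/83 = 13.9% | 10.0% | 4.0 |

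The relative understatement is about 7% to 13% in the first two rows (1 − 20/21.4 and 1 − 20/22.9), nil in the next two, and 16% to 28% in the last two (1 − 10/11.9 and 1 − 10/13.9). If the removed patients had the lower risk, the sign would reverse. The assumed risks drive the result.

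**The case against.** **Early leavers.** A reader might infer that the harms and outcomes of everyone who leaves early disappear. The text does not support that. Exclusion 3 requires that no data exist after chemotherapy, the modified ESAS is collected daily in the first week of each cycle, and adverse events are recorded in the case report form. Most early leavers will have something on file and stay in the FAS. This objection stands. It does not touch exclusion 2, which needs no early exit.

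**Blinding.** A reader might also infer that everyone knows the allocation. The Discussion section says the statistician will be blinded. That limits influence at the analysis stage, but not on exits or eligibility findings that arise at the sites.

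**Window versus population.** The Secondary outcomes text sets when an event counts, and the Statistical analysis section sets who is counted. The two can coexist, so this is a mismatch of scope rather than a logical contradiction. A comparison meant to cover events from randomisation still omits some randomised patients.

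**Eligibility wording.** Exclusion 2 can be read as status at randomisation, which is close to limiting it to pre-randomisation facts. It does not provide for judgement without knowledge of the arm, and it does not justify dropping a treated patient's harms.

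**Transparency.** The exclusions stand openly beside the intention-to-treat phrase, and exclusion 1 is proper. That is fair, but disclosure does not change who is analysed.

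**Record versus analysis.** The events remain in the case report forms, and severe ones reach the ethics committee. The loss is from the comparison, not from the trial record.

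**Conclusion.** The point holds as a stated rule, not as detail left to an analysis plan. The article assigns safety and efficacy to a set that drops ineligible and baseline-only patients after allocation. The certain losses from the safety comparison are the adverse events of treated but ineligible patients, and events before chemotherapy in patients with no later data. Some early on-treatment harms are lost as well if the data in exclusion 3 means questionnaire data only. For efficacy, the exclusions can depend on arm, and nothing stated rules this out.

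It is tempting to conclude that adverse-event rates are understated by a particular percentage. The documents do not support this: they give neither the number removed nor any event risk, and the illustrative figures range from nil to 28% on assumptions alone. With equal risks the rate is unbiased and only events and precision are lost. The correction is worth making because the rule is explicit and cheap to change.

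**What to change.** **Safety.** Report adverse events from randomisation in all randomised patients, regardless of eligibility or questionnaire return, leaving out only those who refuse use of their data. An as-treated table of exposed patients can be added. It should not replace the main table, because a set defined by exposure alone would still miss events between randomisation and first treatment.

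**Efficacy.**
- Keep ineligible patients in the primary set as allocated. Otherwise, limit that exclusion to violations shown by pre-randomisation data and judged without knowledge of the arm.
- Include baseline-only patients by multiple imputation as a sensitivity analysis. Under missing at random they add little to the treatment contrast, so this tests robustness and does not by itself restore the randomised comparison.
- Report every exclusion by arm with its reason. If any exclusion beyond refused data use remains, call the set modified intention-to-treat.

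**Cost.** A change of wording and a little more analysis. Adverse events are already recorded, and the sample size of 83 per arm does not change. Where outcomes are imputed, the interval will be slightly wider.

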### Outcomes

#### Primary outcome

The primary outcome will be the area under curve (AUC) of Functional Assessment of Cancer Therapy – Gastric(FACT-Ga) scale Trial Outcome Index (TOI) during the 3 cycles of chemotherapy.

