This study will use AUCs as the primary endpoint instead of the scores at different time points during the postoperative adjuvant chemotherapy period to decrease heterogeneity. The AUC, as a standard metric in pharmacokinetic analyses, is often used for describing drug concentration. It also has been suggested as a preferred statistic in a variety of clinical settings [41, 42, 49, 50] for embracing all available information to interpret how much improvement after treatment, including evaluating pain relief and enhancement of sleep quality over time [51, 52]. The AUC provides relevant information on how much more improvement in HRQOL, on average, a patient may achieve with acupuncture therapy compared with usual care, rather than the scores at any specific time point.

This study continued to use an open-label design approach, considering the controversy about sham acupuncture control and the clinical meaning of acupuncture. Although sham-controlled trials with blinding are preferred from the perspective of methodology, trials without sham acupuncture have also been recommended recently, because of their emphasis on the practical applicability and increased external validity over treatment efficacy [53]. Sham acupuncture also has some limitations including latent ethics issues brought by unnecessary transportation costs for the sham acupuncture group, uncertain effect of inert control [54, 55], and the lack of consensus on approaches. For these reasons, more and more trials did not include a sham-acupuncture control group [48, 56]. We agree with the opinion of Molassiotis A. and colleagues that shifting the focus from placebo-related issues to those with clinical meanings is appropriate [57]. Although we did not use sham acupuncture in the pilot trial, the differences in quality of life between acupuncture and control groups are over the minimally important difference (MID) [35], indicating that this benefit is clinically meaningful. In addition, in order to control bias as much as possible, the statistician will be blinded to the treatment in this trial.

This study will be the first large-sample, multi-center randomized controlled trial on the efficacy of acupuncture on HRQOL and symptoms during postoperative adjuvant chemotherapy for gastric cancer. We are going to assess the effect of acupuncture, and to compare the difference between LA and HA groups on HRQOL in gastric cancer patients in a rigorous way by an adequately powered trial.

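### Worst-observation-carried-forward as the rule for the primary AUC turns any imbalance in dropout between the open-label arms into a modest apparent treatment difference

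*Protocol article*

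**What the plan says.** The endpoint is stated under Primary outcome: "The primary outcome will be the area under curve (AUC) of Functional Assessment of Cancer Therapy" – Gastric Trial Outcome Index, over three 21-day cycles. Scores are collected at baseline and weekly (Secondary outcomes). For gaps in those scores the Statistical analysis section gives one rule: "Missing data will be imputed using the worst observation carried forward (WOCF) method to calculate the AUC". It offers no rationale, and none appears elsewhere in the article.

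Three other statements bear on the point.

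- **Dropout.** Sample size says "Considering the total dropout rate of 22.41% in our pilot study" and then "we plan to enroll a total of 249 patients to allow a dropout rate of 25" per cent. Neither rate is split by arm.
- **Blinding.** The Discussion says "This study continued to use an open-label design approach, considering the controversy about sham acupuncture control". The outcome is patient-reported, and the statistician is the only party said to be blinded.
- **Visit burden.** The Interventions section gives 21 sessions in the high-dose arm, 9 in the low-dose arm and none in the control arm.

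The full analysis set leaves out, among others, patients with no data after the start of chemotherapy. The rule therefore acts on patients who contribute some weeks and then stop.

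**The concern.** A patient's lowest score to date can only stay level or fall as weeks are added. Filling every later week with it puts that patient's AUC at or below what a stable course would have given. Ordinary week-to-week variation is enough to cause this; no true decline is needed.

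The loss falls only on patients with missing weeks. If one arm has more of them, or loses them earlier, its mean AUC is pulled down for a reason unrelated to efficacy. Equal dropout is not a safe assumption when patients know their allocation and the attendance burden differs as much as it does here. Travel and cost could drive acupuncture patients out, which would hide a benefit. Receiving no study treatment could drive controls out, which would create one. The rule is therefore not reliably conservative.

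As a single imputation, it also passes filled-in scores to the analysis as if they had been observed.

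**Working it through.** **1. The plan's own figures.** The pilot AUCs "were 5402 and 4780 in the acupuncture and control groups, respectively", "with a standardized derivation of 1109". The difference is 5402 − 4780 = 622 units, or 622/63 = 9.9 TOI points averaged over 63 days. With two-sided α = 0.025 and 80% power, the normal approximation gives 2 × (2.241 + 0.842)² × (1109/622)² ≈ 60.4, so 61 per arm. The exact t-test needs 62 (power 80.2%). Then 62/0.75 = 82.7, so 83 per arm, and 3 × 83 = 249. The stated figures reproduce. At 25%, about 0.25 × 83 ≈ 21 patients per arm drop out.

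**2. Formula for the bias.** One dropout's loss is the sum over missing weeks of trapezoid weight × (score the patient would have given − lowest observed score). Under no treatment effect:

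false difference ≈ mean loss per dropout × (dropout proportion in one arm − that in the other).

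With equal proportions and timing it is zero.

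**3. Simulation at nominal 5%.** No true effect, 83 per arm, ten weekly scores, trapezoid AUC. Assumed inputs, none given in the article: AUC SD near 1,090; baseline-to-AUC correlation about 0.84–0.93; a dip of 0–12 points in week 1 of each cycle; dropout unrelated to outcome; every dropout having some post-baseline data. Mean loss per dropout is about 166–370 units.

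| Dropout | False difference (units) | TOI points (÷ 63) | Share of 622 | Type I, baseline-adjusted | Type I, unadjusted t |
|---|---|---|---|---|---|
| 25% v 25% | about 0 | 0 | 0 | about 5% | about 5% |
| 20% v 30% | 17–37 | 0.3–0.6 | 3–6% | about 6–7% | about 5–7% |
| 15% v 35% | 32–76 | 0.5–1.2 | 5–12% | about 8–15% | about 5–7% |

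The formula agrees: 166 × 0.10 ≈ 17 and 370 × 0.10 = 37; 166 × 0.20 ≈ 33 and 370 × 0.20 = 74.

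**4. Why baseline adjustment matters.** The unadjusted standard error is 1109 × √(2/83) ≈ 172, so 32–76 units is only 0.19–0.44 standard errors. Adjustment multiplies the standard error by √(1 − r²): 172 × 0.37 ≈ 63 at r = 0.93, and 172 × 0.54 ≈ 93 at r = 0.84. Pairing the smallest bias with the highest correlation gives 32/63 ≈ 0.51, hence a type I error of Φ(−1.45) + Φ(−2.47) ≈ 8%. Pairing the largest with the lowest gives 76/93 ≈ 0.81, hence about 13%. Both lie within the simulated range.

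**5. Second simulation at the per-comparison 2.5%.** Different assumptions: within-patient SD 5, 8 or 12 points; a smooth mid-treatment dip of 0 or 8 points; dropout uniform over follow-up; 2,000 runs. Loss per dropout was 113–330 units. Baseline-adjusted results:

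| Dropout | False difference (units) | Type I error |
|---|---|---|
| 25% v 25% | about 0 | 2.3–3.3% |
| 20% v 30% | 11–34 | 2.5–3.4% |
| 15% v 35% | 24–63 | 3.7–6.4% |
| 10% v 40% | 33–99 | 5.4–10.1% |

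The Monte Carlo standard error at 2.5% is √(0.025 × 0.975/2000) ≈ 0.35 points. A 10-point gap is therefore hard to tell from no inflation here. Type I error also stays close to nominal with equal dropout, so treating imputed values as observed adds little by itself in this setting.

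**The case against.** The strongest reply is about size. Even a 20-point gap in dropout, which nothing in the article predicts, moves the comparison by roughly one TOI point on a 0–132 scale, against a planned effect of 9.9. The type I figures depend on a high baseline-to-AUC correlation: with it lowered to 0.80 or 0.64, the 15% v 35% case gives about 7–12%. The simulated dropout is also unrelated to outcome, which is the case least favourable to this rule. If patients leave because they are deteriorating, a low filled-in score may be nearer the truth, and a missing-at-random model could be too optimistic. All of this stands. It limits the severity, but it does not justify a primary rule whose validity depends on balanced dropout.

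A reader might infer more than the article supports in four respects.

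- **A contradiction with linear interpolation.** Under Secondary outcomes the AUC is "calculated by linear interpolation, will be used to reflect the repeated measures of HRQOL (FACT-Ga) and symptom burden (mESAS"). That describes how an area is formed from a set of scores, while the imputation rule describes how missing scores are supplied. The two can be sequential steps.
- **Missing sensitivity analyses.** The article names only the per-protocol set, but the statistical analysis plan is not shown and may hold others. Their absence here is not a defect.
- **Scores that recover within each cycle.** The Background says only that the worst decline often falls in the first three months. The week-1 dips are assumptions, and the mechanism works without them.
- **Imputation of the full 25%.** Patients without post-baseline data, and those who refuse analysis, leave the full analysis set and are never filled in. The imputed share may be smaller.

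**Conclusion.** The point holds in a limited form and is a should-fix. The article fixes a single-imputation rule for the primary endpoint that penalises whichever arm has more, or earlier, partial dropout. That follows from the arithmetic of a running minimum and needs no assumption about chemotherapy. The direction in this trial cannot be predicted.

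The size does rest on assumptions: the dropout split by arm, its timing and independence from outcome, the within-patient variation, the baseline correlation, and all dropouts having some post-baseline data. Under them the distortion is nil with balanced dropout, small at a 10-point gap, and about 0.5–1.2 TOI points at a 20-point gap. It is enough to raise the baseline-adjusted error rate clearly, but not to account for an effect of the planned size. The baseline-adjusted analysis is the more exposed one, and the Statistical analysis section does name baseline score as a covariate. The figures do not support a claim that the primary comparison is invalid.

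**What to change.** Make the primary analysis a repeated-measures mixed model on the weekly TOI scores, with arm × week, baseline × week and the two stratification factors (resection extent and neoadjuvant chemotherapy). Take the AUC difference as the trapezoid-weighted sum of the weekly arm differences. An acceptable alternative is multiple imputation of the weekly scores, followed by the AUC and a baseline-adjusted ANCOVA.

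Keep worst-observation-carried-forward as a sensitivity analysis and add a reference-based or delta-adjusted imputation. The new primary analysis assumes missing at random and could flatter an arm whose deteriorating patients leave. Report the amount and timing of dropout by arm. Apply the same approach to mESAS, where the worst score is the highest and the distortion runs the other way on the scale.

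The cost is revised analysis wording and modest programming. No extra patients or assessments are needed, because the weekly scores are already collected, and the same model also serves the average-trajectory secondary outcomes. The change should be made before anyone sees data by arm.

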### Randomization

Patients will be randomly assigned to the HA group, LA group, and control group (1:1:1), using the central randomization system, allowing for full allocation concealment, provided by the Clinical Trial Management System of Xiyuan Hospital, China Academy of Chinese Medical Sciences (CACS). Random assignment will be stratified by resection extent (total/ proximal or distal gastrectomy) and neoadjuvant chemotherapy status (yes or no). An Electronic Data Capture (EDC) system provided by Xiyuan Hospital CACS will be used for research data management. The study coordinator at each site will ensure that the informed consent form has been obtained from each participant before randomization.

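### The two stratification factors are not among the named covariates, and an unadjusted t-test is listed with no rule for the primary outcome: a small, free gain in precision is left unused

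*Protocol article*

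**What the plan says.** The Randomization section of the protocol article states: "Random assignment will be stratified by resection extent (total/ proximal or distal gastrectomy) and neoadjuvant chemotherapy status (yes or no"). With each factor read as two-level, that makes four strata.

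The Primary outcome section defines a continuous endpoint: "The primary outcome will be the area under curve (AUC) of Functional Assessment of Cancer Therapy" – Gastric TOI, over three cycles of chemotherapy.

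The Statistical analysis section gives one list of tests for differences among groups. It includes Student's t-test and "analysis of variance (ANOVA) with least significant difference (LSD) for post hoc test and baseline score as covariate", followed by the χ2 and Fisher's exact tests. The baseline score is the only covariate named. The section does not say which of the tests for continuous data applies to the primary outcome. Neither stratification factor is named in any analysis.

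The Sample size section compares two means without adjustment. The pilot AUCs "were 5402 and 4780 in the acupuncture and control groups, respectively", "with a standardized derivation of 1109", at α 0.025 and 80% power, lead to 62 evaluable patients per arm and 249 enrolled. Tests are two-sided ("All hypothesis tests in this study are 2-sided tests, with an alpha < 0.05").

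**The concern.** Stratified allocation balances the arms on the stratification factors, so the true sampling variability of the difference between arms no longer contains the part of the outcome variance that the factors explain. An analysis that omits them still leaves that part in the error term. If the factors are prognostic, the reported standard error is then larger than the true one, and the test rejects too rarely under the null and under the alternative.

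A second, separate matter is the list of tests. A t-test uses neither the baseline score nor the strata. With no rule for which test is primary, an adjusted and an unadjusted p-value could both be presented as the main result.

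What is at stake is precision on the primary comparisons of each acupuncture arm with control, and clarity about which result counts. The validity of the treatment estimate is not at stake.

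**Working it through.** **Inputs from the protocol article**
- Difference: 5402 − 4780 = 622 (Sample size).
- SD: 1109 (Sample size).
- Alpha per comparison 0.025, power 80% (Sample size); two-sided (Statistical analysis).
- 62 evaluable per arm, 25% dropout, 249 in total (Sample size).

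**Assumed inputs**
- R², the share of the residual AUC variance explained by the strata beyond the baseline score: 0 to 0.10, with 0.20 as an extreme. The documents give no value.
- r, the correlation between baseline TOI and TOI AUC: 0.5 to 0.7. The documents give no value.

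**1. Reproducing the plan's figure.** By the normal approximation, n = 2(2.241 + 0.842)² × 1109² / 622² = 60.4, so 61 per arm. With the exact noncentral t distribution, power is 0.795 at 61 and 0.802 at 62, so 62 per arm reproduces. Then 62 / 0.75 = 82.7, so 83 per arm, and 3 × 83 = 249. The trial was therefore sized for an unadjusted comparison.

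**2. Effect of omitting the strata.** The ratio of the unadjusted to the adjusted standard error is 1/√(1 − R²). The actual two-sided size of a nominal 0.025 test that ignores the strata is 2[1 − Φ(2.241/√(1 − R²))]. Power with adjustment uses the exact t calculation at 62 per arm with SD 1109 × √(1 − R²).

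| Assumed R² | SE ratio | Actual size | Power with adjustment |
|---|---|---|---|
| 0 | 1.000 | 0.0250 | 0.802 |
| 0.02 | 1.010 | 0.0236 | 0.811 |
| 0.05 | 1.026 | 0.0215 | 0.824 |
| 0.10 | 1.054 | 0.0181 | 0.845 |
| 0.20 | 1.118 | 0.0122 | 0.888 |

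Over R² of 0.02 to 0.10 the gain is 0.811 − 0.802 = 0.009 to 0.845 − 0.802 = 0.043, about 1 to 4 percentage points.

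**3. Check by simulation.** Stratified permuted blocks were simulated with 186 patients, three arms and four strata, 3000 runs per scenario. Block size 6 and the stratum shares were assumed. One acupuncture arm was compared with control at two-sided 0.025, first without and then with the strata. The SE and type I error columns come from the runs with no treatment effect.

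| Assumed R² | Mean reported SE, unadjusted | True sampling SD | Type I error, unadjusted / adjusted | Power, unadjusted / adjusted |
|---|---|---|---|---|
| 0.05 | 199 | 195 | 0.023 / 0.025 | 0.806 / 0.822 |
| 0.10 | 199 | 190 | 0.016 / 0.022 | 0.808 / 0.840 |
| 0.20 | 199 | 179 | 0.013 / 0.023 | 0.829 / 0.890 |

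At R² = 0 the two analyses agree (power 0.802 and 0.800). The direction and size match the formulas. The gains are 1.6, 3.2 and 6.1 points.

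**4. The t-test, taken separately.** If it replaced the baseline-adjusted model, its standard error would be 1/√(1 − r²) times that of ANCOVA: 1.155 for r = 0.5 and 1.400 for r = 0.7, or 15% to 40% larger. This loss comes from dropping the baseline score and does not concern the strata.

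**The case against.** - **Scope.** The article condenses a fuller plan, and naming the baseline score does not exclude other covariates. This limits the weight of the point. The article does, however, state a covariate and a list of tests, and that list includes one that uses no covariate, so a later plan would have to add to or depart from the published text.
- **How prognostic the strata are.** The Randomization section gives no reason for choosing the two factors, so it cannot be said that they were chosen because they affect quality of life. Patients are enrolled after resection, so surgery and any neoadjuvant chemotherapy are already past when baseline FACT-Ga is recorded. The baseline score may carry most of their effect, and the gain beyond it could be near zero. This stands.
- **No shortfall.** A reader might infer that the trial is underpowered or that its result would be biased. The documents do not support this. The 62 per arm rests on the unadjusted SD, so 80% power is met without the strata, and the error is on the conservative side.
- **The t-test figures.** A reader might also take the 15-40% as the cost of ignoring stratification. It applies only if the named baseline covariate is dropped, and the sentence can be read as a generic list that also serves categorical data.
- **Selective choice.** The Discussion says that the statistician will be blinded to treatment. This reduces the risk of choosing the test by its result, but it does not say which test is primary.

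**Conclusion.** The point holds as a minor one. The article stratifies by two factors, names neither in the analysis, and does not assign a test to the primary outcome. If the strata explain 2-10% of the residual variance, the standard error is 1-5% too wide, the size of a nominal 0.025 test falls to 0.024-0.018, and about 1-4 power points are forgone at 62 per arm. If they explain nothing beyond baseline, nothing is lost. These sizes rest wholly on the assumed R², because the documents give none. The direction does not depend on its value. The t-test question is separate and conditional: its cost of 15-40% in standard error arises only if that test is used, and only under the assumed correlations.

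**What to change.** State one primary model in the Statistical analysis section: a linear ANCOVA of TOI AUC on arm, baseline TOI, resection extent (total/proximal versus distal) and neoadjuvant chemotherapy (yes/no). Use the same covariates, with the matching baseline score, for the other FACT-Ga AUCs and the mESAS AUC. Remove Student's t-test for these outcomes.

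The cost is a change of wording and two degrees of freedom, with each factor at two levels. Both factors are already recorded at randomisation. No extra data or patients are needed, and the sample size can stay as it is.
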